### Participant enrolment

Participants will be identified from suspected lower GI cancer pathway from NHS trust booking systems (control group) and multidisciplinary team meetings (CRC group) (Fig. 1). Participant eligibility will be confirmed, and participants will be contacted by research staff by telephone at least 24–48 h prior to breath testing. Study details will be provided, including the need to maintain a clear fluid diet for a minimum of 4–6 h prior to testing. The participant information leaflet will be sent to the patient via email or post. Informed consent will be taken by the research staff at the scheduled hospital attendance. Breath sampling will take place at outpatient or pre-assessment clinics for controls and CRC cases prior to any endoscopy or surgery. These in-person endoscopy and surgery pre-assessment appointments are part of patients’ routine care in the study hospitals and therefore patients usually do not need to make additional visits to the hospital for testing. Neither groups will have had bowel preparation prior to their research visit. Using a structured proforma to allow integration of symptoms in the diagnostic model, patient demographics, co-morbidities, medication history, symptoms, cancer characteristics and FIT results are being recorded from either primary or secondary care records (Supplementary material Table S1).

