## Background

In the United Kingdom (UK), colorectal cancer (CRC) is the second most common cause of cancer death, with survival rates amongst the lowest in Europe [1]. If diagnosed early at stage one, the five-year survival is over 90% [2]. However, 23% of patients are diagnosed with advanced disease (stage four) which has a five-year survival of only 10% [3]. Most CRC patients present via the suspected lower gastrointestinal (GI) cancer (30%) or routine (34%) referral pathways, the latter often being associated with significant delay. Twenty-four percent of patients present as an emergency, typically with advanced disease [4].

Early-stage CRC shares many symptoms with common benign conditions and so it can be unclear which patients should be referred for a colonoscopy. Referring all symptomatic patients would overwhelm available resources with demand expected to continue to rise further over the next five years. Annually 1.43 million lower GI endoscopies are performed in the UK, but the diagnostic yield for CRC is lower than 3% [5, 6]. The annual cost of lower Gl endoscopies to the National Health Service (NHS) is estimated to be over £530 million [7]. To improve precision in the early detection of CRC, it is essential to refer patients for colonoscopy who are most likely to have CRC, while not subjecting those at lower risk to an invasive and costly procedure. Therefore, we need sensitive diagnostic tools in primary care that are accurate, easy to perform and accepted by patients.

In the UK, guidelines including the National Institute for Health and Care Excellence (NICE), have recommended the use of the faecal immunochemical test (FIT), which measures the amount of haemoglobin in a stool sample, to triage low-risk symptoms in primary care [8]. Faecal haemoglobin concentrations are known to vary by age, sex, ethnicity, deprivation, cancer stage and iron-deficiency anaemia [9]. Depending on the selected threshold for positivity, sensitivity of FIT for CRC varies between 54 and 93%, specificity between 83 and 95%, with a positive predictive value of 7% in patients with low-risk symptoms [10].

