### COBRA2 study objectives

The objectives of the COBRA2 study are to develop and validate a clinical prediction model (CPM), using an improved technology and methodology, to triage the risk of CRC based on profiles of VOCs obtained from the breath test. The clinical utility of the model for referral for the appropriate reference test will be investigated and compared against the current protocol of referring all patients presenting with symptoms indicative of CRC. We will also perform an exploratory comparison between the breath test and FIT, and assess the performance of combining both tests to detect CRC. This will be followed by a narrow validation study using the same case–control design, to assess the ability of the CPM to distinguish between CRC and non-cancer, and to assess the potential clinical utility of decision rules when used for triaging.

We anticipate an improvement in biomarker identification and quantification due to the use of: (i) updated breath collection device and time-of-flight (TOF) and two-dimensional gas chromatography-mass spectrometry (GC–MS) technology; (ii) calibration curves for target compounds; (iii) avoidance of colonoscopy bowel preparation as a possible confounder, and (iv) additional quality control (QC) steps for biomonitoring thermal desorption (TD) tubes, GC-TOF–MS analysis, and a dedicated laboratory environment, therefore enhancing the lower limits of VOC quantification.

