## Methods

### Study design

COBRA2 is a multicentre, case–control development and validation study. The study involves collection of breath at a single time point from eligible participants and is open to all NHS trusts. The COBRA2 study is sponsored by Imperial College London and has obtained NIHR Clinical Research Network portfolio adoption to support study recruitment. The COBRA2 study commenced in September 2022 and is due to complete by December 2026.

The following groups of participants are being recruited:i)Control group: symptomatic patients who are attending a planned colonoscopy referred under the suspected lower GI cancer pathway. Any patient who is found to have histologically-proven CRC on colonoscopy will be analysed as part of the CRC group.ii)CRC group: patients who either have a confirmed diagnosis of colorectal adenocarcinoma according to a biopsy, or who are due to undergo surgical resection for suspected CRC (with histological confirmation to follow within three months).

The target recruitment for the development of the CPM is 720 patients (470 controls, 250 CRC), aiming for a total of 576 patients (376 controls, 200 CRC) with reliable and complete data (breath test and reference test). For the narrow validation, the target recruitment is up to 250 patients (125 controls, 125 CRC), aiming for 200 patients (100 controls, 100 CRC) with reliable and complete data.

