### Participant eligibility

The following participants are eligible for inclusion:Patients aged ≥ 18 years referred from primary care with symptoms of suspected CRC.Patients with histologically confirmed colorectal adenocarcinoma (stages I-IV) who are treatment naïve (CRC group).

Participants with any of the following will not be eligible for inclusion:i)Previous surgery altering the anatomy of the lower GI tract (e.g., hemicolectomy, anterior resection).ii)Previous treatment (neoadjuvant chemotherapy or radiotherapy or immunotherapy) for CRC.iii)Received bowel preparation for their colonoscopy procedure.iv)History of any other cancer within three years.v)Unable or unwilling to provide informed written consent.

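### Most CRC cases already have a tissue diagnosis when recruited, so sampling before any endoscopy and without bowel preparation cannot hold as written; on the workable reading, earlier work-up is a potential confounder concentrated in cases

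*Protocol article*

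**What the plan says.** Study design gives three ways into the CRC group. The first is "patients who either have a confirmed diagnosis of colorectal adenocarcinoma according to a biopsy". The second is patients "who are due to undergo surgical resection for suspected CRC (with histological confirmation to follow within three months". The third is by reclassification from the control pathway: "Any patient who is found to have histologically-proven CRC on colonoscopy will be analysed as part of the CRC group".

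Participant eligibility lists the CRC group as histologically confirmed and treatment naïve. For all participants it excludes those who "Received bowel preparation for their colonoscopy procedure", with no interval and no exception for cases.

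Participant enrolment says the CRC group is identified at multidisciplinary team meetings and controls from suspected-cancer booking systems. It then says that "Breath sampling will take place at outpatient or pre-assessment clinics for controls and CRC cases prior to any endoscopy or surgery" and that "Neither groups will have had bowel preparation prior to their research visit".

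The COBRA2 study objectives section lists "avoidance of colonoscopy bowel preparation as a possible confounder" among the improvements over COBRA1.

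**The concern.** A patient whose cancer has been confirmed by biopsy and discussed at a team meeting has ordinarily had a lower GI endoscopy. That patient cannot then be sampled before any endoscopy. If the endoscopy was a prepared colonoscopy, the patient also meets the bowel-preparation exclusion. Sites applying the text literally would turn away much of the intended CRC group, and sites applying it loosely would each choose their own meaning.

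The statistical stake lies in the loose reading. Controls are sampled before their index colonoscopy, whereas most cases are sampled after a diagnostic endoscopy. Any VOC that changes with endoscopy, biopsy or preparation, and stays changed until the sample is taken, may then be picked up as a cancer marker. Because exposure would nearly coincide with case status, adjustment across the whole sample would have little overlap to work with. The model would then perform worse in its intended use, which is triage of patients not yet investigated.

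**Working it through.** **1. Number of cases that need a recruitment route.** Inputs from Sample size: sensitivity 90% against 83%, one-sided 5%, 90% power, 20% attrition.

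- Effect size (arcsine method, as in the R package the article names): h = 2·asin(√0.90) − 2·asin(√0.83) = 0.2065.
- n = ((1.645 + 1.282)/0.2065)² ≈ 201. With 200 cases the power is 89.9%.
- Recruitment: 200/0.80 = 250 cases and 376/0.80 = 470 controls.

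The article's figures are reproduced. No sample-size figure is in dispute.

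**2. Which routes fit sampling before any endoscopy and without preparation?**

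| Route into CRC group | Sampled before diagnostic endoscopy? |
|---|---|
| Biopsy-confirmed, found at team meeting | Ordinarily no |
| Suspected CRC awaiting resection | Not stated; number not given, and the CRC-group inclusion criterion names only histologically confirmed patients |
| Control-pathway patient found to have CRC at colonoscopy | Yes |

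Only the third route clearly satisfies both enrolment statements.

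**3. Size of the third route.** Input from Statistical analysis: CRC risk r of about 5–7% on the suspected lower GI cancer pathway. Two readings of the 470 are possible.

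- 470 is the total pathway intake: 470 × 0.05 = 23.5; 470 × 0.07 = 32.9.
- 470 true controls remain after reclassification, 470·r/(1 − r): 470 × 0.05/0.95 = 24.7; 470 × 0.07/0.93 = 35.4.

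That is about 24–35 recruited cases, or 9–14% of 250 (23.5/250 = 9.4%; 35.4/250 = 14.2%). After 20% attrition, 23.5 × 0.8 = 18.8 and 35.4 × 0.8 = 28.3, so about 19–28 are evaluable. The other 215–226 or so must be biopsy-confirmed or suspected cases from team meetings. Filling all 250 from the pathway would need 250/0.07 ≈ 3,570 to 250/0.05 = 5,000 patients, so the design depends on cases already worked up.

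**4. Narrow validation.** On the second reading, 125 × 0.05/0.95 = 6.6 to 125 × 0.07/0.93 = 9.4, so about 7–9 of 125 cases would be sampled before diagnosis. The mix is the same as in development, so a marker of earlier work-up would replicate.

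**5. Precision of a separate estimate.** At a true sensitivity of 90%, the standard error is √(0.9 × 0.1/n): 6.9 percentage points for n = 19, 5.7 for n = 28 and 2.1 for all 200.

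**The case against.** The best defence is that the enrolment sentence should be read respectively: controls before endoscopy, cases before surgery. The article supports this, because it goes on to describe endoscopy and surgery pre-assessment appointments, and its abstract says outpatient sampling is used to avoid bowel preparation. On that reading the rules work and same-episode preparation is avoided in both groups. This stands as a probable intention. It is not what the text says, and it leaves the imbalance in earlier work-up untouched.

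The Background reports that preparation was neither predictive nor a confounder in COBRA1. This also counts, and it means bias cannot be presumed. It does not close the matter. Preparation use in COBRA1 was variable and so could be examined, whereas here prior exposure would nearly coincide with case status. COBRA2 also uses more sensitive measurement and screens for additional VOCs.

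The authors state that broad validation is required, and the Discussion describes COBRA3 in patients whose diagnosis is unknown. That study could expose an artefact, but only after the model has been built and narrowly validated.

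Fig. 1 and Table S1 are not shown, so some of the dates requested below may already be recorded.

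A reader might go further and infer three things that the documents do not support:

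- That work-up VOCs will certainly be selected as cancer markers. Neither the interval from endoscopy to sampling nor the persistence of any effect on breath is given.
- That all 200 evaluable cases are exposed. The reclassified cases are not, and the suspected-CRC route is of unknown size.
- That only 30% of recruited cases share the controls' pathway. The statement "Most CRC patients present via the suspected lower gastrointestinal (GI) cancer (30%) or routine (34%) referral pathways" describes how CRC patients present in general, not who attends these clinics. Referral route is a secondary point worth recording.

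**Conclusion.** The contradiction in wording is established. Study design, Participant eligibility and Participant enrolment cannot all be applied literally to most of the CRC group. The claim in the objectives that preparation is avoided as a possible confounder is supported only for preparation in the same episode as the sample.

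On the workable reading, prior endoscopy, biopsy and often preparation are a potential confounder. Their direction and size are unknown. Only about 24–35 of 250 recruited cases are clearly free of them, and the narrow validation cannot reveal an effect.

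This rests on four assumptions: a biopsy diagnosis ordinarily follows an endoscopy; the 5–7% risk applies to the patients recruited as controls; attrition is 20% in every route; and controls have had no comparable recent work-up. The share of diagnostic endoscopies done with full preparation is not given, so exposure to preparation may be lower than exposure to endoscopy.

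**What to change.** 1. Reconcile the sections by stating which procedure and which preparation the timing rule and the exclusion refer to, so that sites can apply them to both groups in the same way.
2. Limit the claim in the objectives to same-episode preparation, and acknowledge sampling of cases after diagnosis as a limitation.
3. Ensure that date and type of last endoscopy, biopsy and bowel preparation, and referral route, are captured for every participant, if the proforma does not already do so.
4. Flag cases sampled before diagnosis and report their sensitivity separately at the final fixed threshold.
5. As a sensitivity analysis within cases, examine whether the selected VOCs or the model score vary with prior preparation or time since it. VOCs should not be removed automatically on this basis: time since work-up may track stage or treatment route, and true markers could be lost.

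The cost is a wording clarification, a few dated fields and one stratified and one sensitivity analysis. The drawback is imprecision: with about 19–28 evaluable cases, the standard error of the pre-diagnosis sensitivity is roughly 6–7 percentage points, so it can show a large discrepancy but not exclude a moderate one.

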**Fig. 1 Fig1:**
[figure not shown]
Recruitment pathway for breath testing in control and colorectal cancer cases. Abbreviations: CRC, colorectal cancer; CRN, Clinical Research Network; FIT, faecal immunochemical test; MDT, multidisciplinary team; TD, thermal desorption; VOCs, volatile organic compounds

### Breath sample collection

Participants will be asked to provide a breath sample (up to 2 L) by exhaling directly into a single-use breath collection bag via a mouthpiece that is subsequently sealed. A breath sampling system will pump breath from the bag onto two TD tubes, with a double-bed sorbent phase composed of Tenax TA/Carbograph 5TD (Markes International Ltd, Llantrisant, UK), within an air-tight system at a controlled flow rate of 200 ml/min [29]. This process will be repeated, and the room air will then be sampled using two further TD tubes to control for potential background environmental contamination. The tubes will be immediately sealed with airtight brass caps and transported to the Imperial VOC laboratory for same day mass spectrometry analysis. When analysis is not possible within 48 h, TD tubes will be dry purged prior to storage at −80 °C for subsequent analysis.

### Volatile organic compound analysis

Breath and room air samples will be analysed, with established Standard Operating Procedures at Imperial College London, using TD-GC-ToF–MS instruments (Markes TD100-XR-Agilent 6890-BenchTOF Select, SepSolve, UK) equipped with polar and mid-polar columns. Two TD tubes will be analysed using both mid-polar and polar GC-ToF–MS. VOCs will be recollected and analysed using a two-dimensional TD-GCxGC-ToF–MS (TD100-XR-Agilent 7890-Sepsolve modulator-BenchTOF Select-eV, Sepsolve, UK) for robust structural identification of VOCs. The acquired spectra will be compared against the National Institute of Standards and Technology (NIST) mass spectral library and authentic standards will be then used for chemical verification of compounds. Data will be extracted, pre-processed and quality controlled using ChromSpace (Markes, UK) and in-house scripts. The VOCs discovered during this analysis will also be compared with previously identified VOCs from the COBRA1 study. All study data will be collected according to the Data Protection Act 2018 and in line with General Data Protection Regulation (GDPR).

### Quality control

QC mechanisms in our laboratory include: (i) coding of TD tube usage and background level check prior to tube transport to site; (ii) transport of tubes on a weekly basis via dedicated couriers using standardised inert transport containers; (iii) upon arrival to laboratory, tubes are barcoded along with anonymised patient ID to ensure full traceability; (iv) tube storage in dedicated prenumbered slots to facilitate sample identification pre-analysis; and (v) electronic audit trail of tube use within a secure Laboratory Information Management System (LIMS). Breath sample analysis includes (i) daily QC of TD-GC-ToF–MS instruments to evaluate the precision of measure of VOCs within the run and in-between runs; (ii) ensuring the presence of quality breath sample using a threshold for a reference endogenous compound; (iii) coding and linking mass spectra that pass QC standards to metadata; and (iv) automated high throughput system.

### Statistical analysis

The COBRA2 study is a development and narrow validation study which follows the validation strategy described by Cowley et al. [30] and Transparent Reporting of a multivariable prediction model for Individual Prognosis Or Diagnosis (TRIPOD) guidelines [31]. This method ensures the development of a rigorous and robust CPM that maximises the potential benefit on patient care and decision-making in clinical practice. For development and validation, we use a case–control design for efficiency given that CRC has a low prevalence in the population. Patients referred on the suspected lower GI cancer pathway have a CRC risk of approximately 5–7% [32]. We will use statistical methods for model development and validation. Initially, we will confirm previously identified VOCs using enhanced measurement methods. Using VOCs from COBRA1 as a base, a screening step will identify the most promising additional predictors. Then logistic regression methods will be used to develop a model based on the breath test alone, including all identified VOCs. To reduce over-fitting, we will use model reduction methods such as the elastic net, least absolute shrinkage and selection operator (LASSO) or Harrell’s stepdown approach [33]. For internal model validation, the following will be used [33, 34]:10-fold cross-validation and median values of the performance measures across folds.For calibration, predicted risks of CRC will be plotted against the observed risks.For overall predictive performance Mean Absolute Prediction Error will be estimated (0%: perfect prediction, 100%: no predictive value).For discrimination, the non-parametric AUROC will be calculated, and the threshold that achieves the best trade-off between sensitivity and specificity will be extracted.

For final models, we will use logistic regression modelling to also include patient and clinical characteristics. We will assess linearity of relationships between CRC risk and continuous variables, and explore categorical variables and two-way interactions, including interactions with the breath test. All candidate predictors will initially be entered into the model, before simplification based on Wald statistics (significance < 0.05), size of the predictive weight (odds ratio) and clinical opinion. If there are missing patient or clinical characteristics, we will consider using imputation techniques [35].

In addition to the statistical methods, random forest and deep neural networks (DNNs) will be explored to assess whether they can improve model predictions. Random forest will be used to construct multiple decision trees from data subsets and combine their predictions to identify key VOCs that predict CRC. DNNs will be employed to model nonlinear relationships in the VOC data. Data analysis and data cleaning will be carried out using the statistical computing language R [36]. We will also calculate the sensitivity, specificity and AUROC of the FIT results (where available). We will compare these quantities informally since there will not be sufficient power for a statistical comparison. We will then assess whether incorporating FIT into the final CPM improves diagnostic performance.

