Currently, there is limited published data which has assessed the performance of breath VOCs in the detection of CRC [17–23]. In these studies, the performance of VOC-based tests was similar to those of existing stool-based immunohistochemical and DNA tests [24]. However, the potential impact of these studies was limited by sample size, unstandardised methods lacking validation and the non-human origin of some reported VOC markers. In 2022, we completed a discovery study, COlorectal BReath Analysis 1 (COBRA1), which showed the proposed breath test has the potential to detect CRC [25]. A diagnostic model to detect CRC was developed from 855 symptomatic patients (709 controls, 146 CRC) with an area under the receiver operating characteristic (AUROC) curve (± standard error) of 0.91 ± 0.01, sensitivity of 83 ± 2%, specificity of 88 ± 1% and negative predictive value of 96%. This was based on a panel of 14 VOC biomarkers (along with body mass index) identified for CRC. COBRA1 had some limitations that should be acknowledged. This includes heterogeneity of populations and variable use of colonoscopy bowel preparation amongst participants included in the study (although this was not found to be a predictive feature or confounding factor in the VOC-based model). Participants were not sampled if they were receiving any concurrent chemotherapy, but they were not excluded if they had any prior chemotherapy, radiotherapy, or immunotherapy. In addition, the technology was not available at the time to perform robust structural and chemical validation of the VOCs using two-dimensional gas chromatography.

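### The stated analyses do not isolate the accuracy that breath adds to patient characteristics: VOCs are selected on breath alone, and no characteristics-only comparator is described

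*Protocol article*

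**What the plan says.** All references are to the protocol article.

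- **Order of modelling (Statistical analysis).** Previously identified VOCs are confirmed first. Then "Using VOCs from COBRA1 as a base, a screening step will identify the most promising additional predictors". Next, "logistic regression methods will be used to develop a model based on the breath test alone, including all identified VOCs", reduced by elastic net, LASSO or stepdown. Only after that: "For final models, we will use logistic regression modelling to also include patient and clinical characteristics".
- **Final models (same section).** The plan explores "two-way interactions, including interactions with the breath test". It adds: "All candidate predictors will initially be entered into the model, before simplification based on Wald statistics (significance < 0.05"), with the odds ratio and clinical opinion as further criteria.
- **Source of the groups (Participant enrolment).** "Participants will be identified from suspected lower GI cancer pathway from NHS trust booking systems (control group) and multidisciplinary team meetings (CRC group"). The article states no matching or balancing on age, sex or anything else.
- **Data available (Participant enrolment).** "patient demographics, co-morbidities, medication history, symptoms, cancer characteristics and FIT results are being recorded".
- **Stated comparisons.** FIT alone is evaluated where available and compared informally, and FIT is then added to the final prediction model (Statistical analysis). Clinical utility is compared with referring every symptomatic patient (COBRA2 study objectives).
- **Earlier model (Background).** COBRA1's AUROC of 0.91 rested on "a panel of 14 VOC biomarkers (along with body mass index"), so it was not a breath-only figure.

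**The concern.** Controls come from booking systems for the suspected-cancer pathway, and cases from multidisciplinary team meetings. The two groups may well differ in age, sex, body mass index, medication or co-morbidity. A VOC that follows one of these will differ between the groups even if it carries no information on cancer, and a screening step confined to breath data cannot tell the two situations apart. The narrow validation uses the same case-control design, so it would tend to repeat a systematic imbalance rather than reveal it.

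The article presents breath as a first-line triage test in primary care, where age, sex and symptoms are already known. The useful quantity there is what breath adds to them. The stated increments run the other way: characteristics are added to breath, and FIT is added to a model that already contains breath.

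**Working it through.** **1. Which comparisons are stated**

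| Model or comparison | Stated? |
|---|---|
| Breath alone | yes |
| Breath plus characteristics (final model) | yes |
| FIT alone, where available | yes |
| Final model plus FIT | yes |
| Characteristics alone | not described |
| Characteristics alone against characteristics plus breath | not described |

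The gain from breath is the AUROC of the final model minus the AUROC of characteristics alone. The second term is not among the stated analyses.

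**2. The plan's own figures**

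The sample size reproduces with the one-sided 5% arcsine method, n = ((1.645 + 1.282)/h)².
- Sensitivity 90% against 83%: h = 0.2065, n = 200.9 (plan: 200).
- Specificity 85% against 78%: h = 0.1810, n = 261.4 (plan: 262, raised to 376 controls).

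These figures are not in dispute. The 200 cases and 376 controls are used below.

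**3. How large the inflation could be**

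The documents give no case-control difference in age and no VOC-age correlation, so the following values are assumptions.
- d: difference in one covariate between cases and controls, 0.3 to 1.0 SD.
- r: correlation of each VOC with that covariate, 0.2 to 0.5.
- k = 14 VOCs, the size of the COBRA1 panel, with no link to cancer given the covariate.

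Formulas (binormal model):
- Covariate alone: AUROC = Φ(d/√2).
- Proxy panel: D² = k(rd)²/[(1 − r²) + kr²], AUROC = Φ(D/√2).

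Example with d = 0.5 and r = 0.3: D² = 14 × 0.0225/(0.91 + 1.26) = 0.145, so AUROC = Φ(0.381/1.414) = 0.606.

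| d | Covariate alone | Panel, r = 0.2 | Panel, r = 0.3 | Panel, r = 0.5 |
|---|---|---|---|---|
| 0.3 | 0.584 | 0.551 | 0.564 | 0.576 |
| 0.5 | 0.638 | 0.585 | 0.606 | 0.626 |
| 0.8 | 0.714 | 0.634 | 0.667 | 0.696 |
| 1.0 | 0.760 | 0.666 | 0.705 | 0.739 |

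**4. Would such VOCs be selected?**

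For one proxy VOC in an unadjusted two-sided 5% screen, the noncentrality is rd/√(1/200 + 1/376) = rd/0.0875. The 5% screen is also an assumption, because the article gives no screening rule.
- d = 0.3, r = 0.2: probability of passing 0.11.
- d = 0.5, r = 0.3: 0.15/0.0875 = 1.71, probability 0.40.
- d = 0.8, r = 0.5: probability 0.995.

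**5. Against the accuracy the study looks for**

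- COBRA1's 0.91 corresponds to D = √2 × Φ⁻¹(0.91) = 1.90. A single covariate would have to differ by about 1.9 SD to reach it alone.
- The targets of 90% sensitivity and 85% specificity correspond to Φ((1.282 + 1.036)/1.414) = 0.95 in the same model.
- If proxy VOCs and cancer-related VOCs are independent within groups, their D² values add. Take an observed breath-alone AUROC of 0.91 (D² = 3.595). Removing a proxy part of D² = 0.145 (d = 0.5, r = 0.3) leaves Φ(√(3.450/2)) = 0.905. Removing 0.824 (d = 1.0, r = 0.5) leaves Φ(√(2.771/2)) = 0.88.
- At an observed 0.80 (D² = 1.417), the lowest AUROC in the article's precision statement, the same two removals leave 0.79 and 0.71.

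Under these assumptions one imbalanced covariate matters little when true accuracy is high, and more when it is moderate. Several imbalances together could add more.

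**The case against.** **The final models already adjust.** Breath and characteristics are entered together, with interactions. A panel that merely tracked age would have an expected adjusted odds ratio near 1 and would usually be dropped at the 5% level. This stands. A reader might infer that the accuracy cannot be attributed to breath at all, and the documents do not support that. What the adjusted test does not give is a gain in AUROC or in sensitivity, and it is applied to VOCs already chosen, without adjustment, in the same data.

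**Silence is not absence.** The article is condensed and no SAP is shown. A reader might infer that no model without VOCs will be fitted. The supportable statement is only that no characteristics-only model is described. FIT alone is in any case an estimate without VOCs. Likewise, matching is not stated, which is weaker than being ruled out. The order of modelling is stated, however, and so are the comparisons listed above.

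**A proxy panel would not pass.** A reader might infer that a panel tracking age could be reported as a breath test of useful accuracy. The illustration does not show this. With 200 cases and 376 controls, an AUROC of 0.60 has a standard error of about 0.025 and would look clearly better than chance, but the study's targets are far higher.

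**Selection on breath first is a legitimate strategy.** A prediction model may use predictors that correlate with age. Controls are symptomatic patients, and the authors say that broad validation must follow. This stands too. Adjusting the VOC selection is therefore a matter of judgement, whereas reporting the gain from breath is not tied to either strategy.

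**Conclusion.** The point holds in a limited form. The stated analyses give a breath-alone accuracy and, in the final models, an adjusted association for breath. They do not estimate how much AUROC or sensitivity breath adds to characteristics already recorded. Selection on breath alone, with groups from different sources and no stated matching, means that the breath-alone figure may be partly inflated.

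The amount is unknown. Across the assumed range (one covariate, d = 0.3 to 1.0 SD, r = 0.2 to 0.5) a pure proxy panel reaches 0.55 to 0.74, so one such difference could contribute to an AUROC near 0.91 but would not explain it. These figures rest on the binormal model and on assumed differences, not on data in the documents. The point is a worthwhile improvement to the analysis; it does not invalidate the design.

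**What to change.** **Change to the Statistical analysis section**

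1. Add a logistic model with recorded patient and clinical characteristics only, for example age, sex, BMI and symptoms. BMI is assumed to be on the data-collection form (Table S1 is not shown). Cancer characteristics must stay out because they exist only for cases.
2. Report the gain from adding the breath score to that model: the difference in AUROC and the difference in sensitivity at a fixed specificity, each with a confidence interval. Use the same cross-validation folds for both models and repeat the comparison in the narrow validation sample.
3. As a sensitivity analysis only, repeat the VOC screening and reduction with age, sex and BMI in the model, and show which VOCs remain.

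**Cost.** A little more analysis, with no extra patients or samples. Breath's contribution may look less favourable than the breath-alone AUROC. The gain will still describe this case-control sample, so it should be estimated again in the planned broad validation.
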